#### Methods in analysis to handle protocol non-adherence and any statistical methods to handle missing data {20c}

All researchers will be trained referring to the same training protocol. Missing intraoperative data, if any, will be obtained from the electronic hospital files. Postoperative evaluation at specified time points is mandatory, and missing postoperative data are not to be anticipated. Analyses of all outcomes will be performed according to the intention-to-treat principle, and once enrolled, all participants will be analyzed, regardless of the findings.

## Discussion

Dreams are a remarkable experiment in psychology and neuroscience, conducted every night in every sleeping person. They show that the human brain, disconnected from the environment, can generate an entire world of conscious experiences by itself. The occurrence of dreams is also one of the common phenomena of anesthesia and sedation. The occurrence of dreams during general anesthesia has been reported in the literature. The dream after anesthesia refers to the patient’s experience after the induction of anesthesia to the beginning of the waking phase. Domestic scholars have conducted research on the effects of short-town intravenous anesthesia and specific anesthetics on dreams of adult receiving surgery, which found that the incidence of adult dreams is about 18% ~ 49.7% [19, 20]. Among them, different anesthesia drugs, operation site, operation time, and so on are all the influential factors leading to the occurrence of dreams. Previous hypothesis also thought that dreaming occurs intraoperatively and is related to light or inadequate anesthesia [21, 22]. In order to verify this previous hypothesis, we designed a randomized, observer- and patient-blinded, controlled clinical trial, which compared the effects of different maintenance doses of propofol on patients’ dreams and analyzed the related factors affecting dreams. A recent study has shown that depression and anxiety assessed by Beck anxiety/depression inventory can predict a negative dream during natural sleep [23]. Similarly, we assessed preoperative anxiety level to see if patients with different preoperative anxiety states were associated with different dreams generated during anesthesia. In our trial, the subjective outcomes including HADS, Ramsay scale, modified Brice questionnaire, and awareness classification will be assessed. In this way, the effect of different dose of propofol maintained during the surgery on the incidence of dreaming of patients will be evaluated from multiple perspectives.

Our study has some limitations. First, since all the patients were hospitalized, we only scored the preoperative anxiety during the perioperative period but did not evaluate the daily long-term psychological base state and the degree of dreaming under natural sleep. Second, the study was part of a single-center survey, multicenter survey still need to be studied.

## Conclusion

In conclusion, the results of our trial are expected to demonstrate the proportion of patients in the HBIS group who had dreams during the surgery vs that of patients in the LBIS group and whether there are patient-reported awareness during anesthesia. Through all the patients who reported dreaming during the surgery, we are aimed to explore the proportion of those who reported having pleasant dreams in the LBIS group vs that of patients in the HBIS group, to further compare whether there is a difference in the dosage of propofol between the two groups, and to analyze the factors associated with different postoperative dream generation. In summary, according to the study results, we hope to provide a basis for good perioperative experience and better postoperative recovery of patients in clinical practice.

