### Randomization, study intervention, and blinding {16c, 17a}

All patients were randomly divided into either the low bispectral index (LBIS) group (*n* = 62) or the high bispectral index (HBIS) group (*n* = 62). Randomization was conducted using a random-permuted block randomization algorithm. The randomization sequence was kept in sealed envelopes. On the day of surgery, the investigator opened the envelope and prepared the study drug according to the allocated group and delivered it to the operating room wrapped with opaque paper. The result of the group allocation was not opened until the time of data analysis. In all cases, anesthesia was conducted by the same anesthesiologist and outcome assessments were carried out by another anesthesiologist, and both were blinded to the group allocation. In the LBIS group, BIS was maintained between 40 and 50 during the operation, and in the HBIS group, BIS was maintained between 50 and 60 for maintenance. The patients, attending anesthesiologists, surgeons, and data collectors were all blinded to patient group assignment.

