#### Time and method of dreaming investigation

After emergence from sedation and orientation recovery, a modified Brice questionnaire was immediately used to evaluate the incidence of dreaming. Patients who reported dreaming were required to complete an awareness classification regarding the awareness level of their dreams.

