#### Modified Brice questionnaire [16]

What was the last thing you remember before going to sleep?What was the first thing you remember from when you woke up?Can you recall anything between?Did you have any dreams while under anesthesia?How did you feel about your dream: pleasant, indifferent, or unpleasant?

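### The exploratory LBIS v HBIS comparison of pleasant dreams is made among dreamers only, so a difference could reflect who dreams and not any effect of depth on dream quality

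*Protocol article*

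**What the plan says.** The Conclusion lists what the trial is expected to show. First comes dream incidence: "the proportion of patients in the HBIS group who had dreams during the surgery vs that of patients in the LBIS group". Next comes dream quality: "Through all the patients who reported dreaming during the surgery, we are aimed to explore the proportion of those who reported having pleasant dreams", and the contrast is "in the LBIS group vs that of patients in the HBIS group". The denominator of the second comparison is therefore the patients who dreamed.

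Three other statements bear on it.
- **Timing.** Under the heading on the time and method of the dream investigation: "After emergence from sedation and orientation recovery, a modified Brice questionnaire was immediately used to evaluate the incidence of dreaming". Dream status is thus known only after the randomised depth has been delivered.
- **Hypothesis.** The Discussion, like the Abstract and Introduction, gives the idea under test as "dreaming occurs intraoperatively and is related to light or inadequate anesthesia".
- **Quality item.** The questionnaire asks "How did you feel about your dream: pleasant, indifferent, or unpleasant", which only a patient who reports a dream can answer. The preceding item, whether there was any dream, is put to everyone.

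On the analysis population, section {20c} says "Analyses of all outcomes will be performed according to the intention-to-treat principle" and adds that every enrolled participant is to be analysed whatever is found.

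**The concern.** Randomisation makes the two groups of 62 comparable. It does not make the dreamers in one group comparable with the dreamers in the other unless depth has no influence on who dreams, and the trial was set up because the investigators suspect that it does. If lighter anaesthesia brings in additional dreamers whose dreams are pleasant more or less often than the rest, the pleasant share among dreamers moves although depth has altered nobody's dream.

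The article itself gives a reason why composition could matter. Its Discussion cites work in which anxiety and depression predicted negative dreams in natural sleep. If depth changes the mix of anxious and calm patients among dreamers, the pleasant share changes with it.

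At stake is the interpretation of a patient-experience result. The Statistical analysis section gives general rules for testing categorical data at the 0.05 level, plus a logistic regression involving dream quality, and states no caution for a subgroup defined after randomisation.

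**Working it through.** The article gives no figure for pleasantness, so there is none to reproduce. Its sample-size calculation concerns propofol dose and does not bear on this point.

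**Inputs from the article.** 62 patients per arm (Randomization section); dream incidence of about 18% to 49.7% in other studies (Discussion).

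**Assumed inputs.** All pleasantness rates, and the dream rates in each arm.

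**1. Basic illustration.** Under LBIS 20% dream, 70% of them pleasantly. HBIS leaves those dreams as they are and adds 20% of patients as dreamers, 40% of them pleasantly.

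| Share of all randomised | LBIS | HBIS | HBIS − LBIS |
|---|---|---|---|
| Pleasant dream | 0.20 × 0.70 = 14% | 0.14 + 0.20 × 0.40 = 22% | +8 points |
| Non-pleasant dream | 0.20 × 0.30 = 6% | 0.06 + 0.20 × 0.60 = 18% | +12 points |
| No dream | 80% | 60% | −20 points |

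Among dreamers: LBIS 0.14/0.20 = 70%, HBIS 0.22/0.40 = 55%, a difference of −15 points. The effect of depth on those who dream in either arm was set to zero, so all 15 points come from selection.

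**2. What drives the size.** Let pL and pH be the dream rates, qA the pleasant share in patients who dream under either depth (unaffected by depth), and qI the pleasant share in the added dreamers. If HBIS only adds dreamers, the spurious difference is

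(pH − pL)/pH × (qI − qA).

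With pL = 20%, pH = 40% and qA = 70%, the first factor is 0.20/0.40 = 0.5:
- qI = 40%: 0.5 × (−0.30) = −15 points
- qI = 55%: 0.5 × (−0.15) = −7.5 points
- qI = 70%: 0
- qI = 85%: 0.5 × (+0.15) = +7.5 points

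The distortion can go either way, and it is nil if the added dreamers resemble the others or if nobody is added.

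**3. Ends of the incidence range quoted in the article.** With pL = 18%, pH = 49.7%, qA = 70% and qI = 40%, HBIS dreamers show (0.18 × 0.70 + 0.317 × 0.40)/0.497 = 0.2528/0.497 = 50.9%, against 70%. The difference is −19.1 points, again with no true effect.

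**4. Equal incidence is not a safeguard.** Suppose 30% dream in each arm: 10% dream under either depth (60% pleasant under LBIS, 70% under HBIS), 20% dream only under LBIS (80% pleasant), and 20% only under HBIS (40% pleasant). Then LBIS shows (0.10 × 0.60 + 0.20 × 0.80)/0.30 = 73.3% and HBIS (0.10 × 0.70 + 0.20 × 0.40)/0.30 = 50.0%. Observed incidence rates that look alike would not show that the dreamers are alike.

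**5. Precision.** 62 × 0.18 ≈ 11 and 62 × 0.497 ≈ 31 dreamers. For 70% v 50% with 11 and 31 patients, the 95% half-width is 1.96 × √(0.70 × 0.30/11 + 0.50 × 0.50/31) ≈ 0.32, or 32 points; power is about 19%.

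**The case against.** The comparison is worded as exploratory and follows the incidence comparison, which keeps all randomised patients. Pleasantness has no meaning without a dream, so a conditional summary is a natural description. No sentence names a between-arm test or a causal claim for this result. Since incidence per arm will also be reported, a reader could multiply the two and recover pleasant dreams out of all randomised. The statistical analysis plan is not shown and may label the comparison suitably.

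Much of this stands, and it limits the weight of the point. It does not remove it: the article itself states the denominator, and exploratory wording does not make the dreamers comparable.

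Four stronger readings are tempting, and the documents do not support them.
- **The effect reverses sign.** In the basic illustration, 55% v 70% and 22% v 14% answer different questions: quality given a dream, and frequency of pleasant dreams. Opposite signs there are not one effect reversing. A reversal of a true effect in those who dream under either depth can be constructed: with pL = 18% and pH = 49.7%, a rise from 70% to 80% in them appears as (0.18 × 0.80 + 0.317 × 0.40)/0.497 = 54.5% v 70%. That needs further assumed rates.
- **HBIS is better by 8 points.** In the same example non-pleasant dreams rise by 12 points, and the protocol nowhere says that a pleasant dream is preferable to none.
- **The plan contradicts its intention-to-treat statement.** That sentence stands under non-adherence and missing data, and patients stay in their allocated arm. The dreamers-only denominator sits uneasily with the promise to analyse everyone; it is a tension to reconcile, not a clear contradiction.
- **The dreamers are a subgroup created by the intervention.** That takes the hypothesis as fact. If depth does not affect who dreams, this bias disappears.

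**Conclusion.** The point holds as a limited one. The planned LBIS v HBIS comparison of pleasant dreams conditions on an outcome that arises after randomisation and that the trial expects its intervention to change. A difference among dreamers cannot by itself be read as an effect of depth on dream quality. Under the assumed rates the spurious difference is 15 points (55% v 70%), and about 19 points at the ends of the incidence range quoted in the article. Both figures rest on assumed pleasantness rates and on HBIS adding dreamers who differ from the rest, so they show what is possible and do not predict the result. With roughly 11 to 31 dreamers per arm, the comparison would also be imprecise. The comparison of dream incidence is not affected.

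**What to change.** Make the between-arm comparison in all randomised patients, with each patient in one of four unordered categories: no dream, unpleasant, indifferent, pleasant. The categories should not be ranked, because an ordering that puts no dream below an unpleasant one has no basis in the protocol. Report pleasant dreams and unpleasant dreams each as a proportion of all randomised, with risk differences and 95% confidence intervals.

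Keep the dreamers-only table as description, without a between-arm P value or causal wording. If the logistic model for dream quality is fitted in dreamers and includes treatment group, the same caution applies to that coefficient. Add a sentence to section {20c} saying how the intention-to-treat statement applies to outcomes that exist only for dreamers.

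The cost is analysis-plan wording and a change of denominator; the questionnaire already supplies every category. By the article's account allocation stays closed until analysis, so the change can be made blind if that is still the case; otherwise it should be reported as made afterwards. One small downside: the all-randomised proportions combine how often patients dream with how they feel about the dream, so they should be read beside dream incidence.

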## Trial status

The participant recruitment was finished and data collection are in progress. Protocol version number is 1.0 and date: 2021.11; the date recruitment began on November 30, 2021, and an estimate of the date would be April 30, 2022, when recruitment will be completed.

## Data Availability

N/A.
